### Inclusion and exclusion criteria

Participant inclusion criteria are as follows: (1) age 70 years and older and (2) a minimum baseline six-item De Jong loneliness score of 2/6, corresponding to loneliness or high risk of loneliness [13]. We will accept referrals from participating ED and clinics as well as self-referrals from participants to improve recruitment.

We will exclude individuals (1) living in nursing homes; (2) with significant cognitive impairment as assessed by the Adamis capacity assessment [14, 15]; (3) with difficulty communicating (i.e., critically ill, unconscious, unable to communicate in English, speech impairment or otherwise unable to provide consent); (4) without access to a telephone; and (5) admitted to hospital for > 72 h. Volunteers will be excluded if they are less than 19 years of age and, in the case of intergenerational volunteers, if they are over 39 years of age. Same-generation peer support volunteers less than 60 years of age will be excluded.

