### Randomization and blinding

We will use a computerized number generator to randomize to the three study arms in blocks of three, stratified by referral source. This will be an open-label trial. We will use an outcome assessment blinding process developed in our previous trial: outcomes assessors are blinded to the intervention group and record the primary outcomes at the start of follow-up calls to prevent accidental unblinding. Participants are also instructed not to reveal which intervention to any research staff, and any instances of unblinding will be documented by the outcome assessor. No formal auditing process is implemented for this trial.

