### Analysis

All analyses will use SAS Version 9.4 (SAS Institute, Cary, NC, USA). A two-sample two-sided test of proportions will be used to assess the primary outcome of loneliness in the control group versus the intergenerational HOW R U?, and the control group versus the same-generation peer support HOW R U? intervention. Improvements in the binary outcome of the loneliness category of the De Jong Loneliness Scale will be assessed using a logistic regression model, and results will be reported as odds ratios with the corresponding 95% confidence intervals. The variance inflation factor (VIF) will be calculated to assess for multicollinearity before the logistic regression model is built such that if two variables are highly correlated (i.e., VIF > 4 or tolerance < 0.25), only one of the two variables is retained for the final model. To compare the secondary outcomes, they will be reported as means with corresponding 95% confidence intervals.

Potential missing data will be managed as follows. For logistic regression, participants with more than 15% missing data for confounding variables will be excluded from the analysis. Note that in the main trial, less than 5% of participants would have been excluded. For participants with less than 15% missing data, we will use imputation for confounding variables. Participants with missing outcome data will be excluded from analysis (i.e., lost to follow-up). Note that after two-thirds of the participants have been enrolled, we will assess the loss-to-follow-up rate and adjust the enrollment accordingly. For example, if the lost-to-follow-up rate is 20%, we will increase the enrolment by 20%. To manage protocol nonadherence, participants will be analyzed using intention-to-treat analysis regardless of their adherence to the protocol.

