## Discussion

We describe a protocol for a three-arm RCT assessing the effectiveness of an intergenerational telephone support intervention compared to the same-generation peer support intervention and to a common control group in reducing SIL for the older adult population after discharge from the ED.

The ED represents an important but unexploited setting to screen for SIL and initiate social interventions. Prior studies have supported the benefit of intergenerational interventions in reducing SIL in older adults in long-term care homes as well as those who were solicited in the community, though these benefits have not been assessed in the post-ED discharge setting, nor have they been compared to the same-generation peer support interventions [7].

The aging process is experienced diversely by different individuals. Thus, a suite of interventions to address SIL may be beneficial. Intergenerational interventions are a potential alternative to peer support interventions for reducing SIL while potentially benefiting student participants as well [7, 26]. In addition, younger intergenerational volunteers could expand the pool to recruit volunteers and broaden the impact of any intervention. Assessing the effectiveness of the intergenerational HOW R U? intervention will inform whether it is beneficial in reducing SIL and whether it can be applied in the ED setting, and increase our understanding of generativity as a modifiable construct for the development of future social interventions.

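### Randomisation is stratified by referral source but the stated primary test is not; the test is conservative and gives up a little power if the source predicts improvement

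*Protocol article*

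**What the plan says.** **Allocation.** Under Randomization and blinding, the protocol article allocates participants to three arms, using blocks of three, "stratified by referral source". No other stratification factor is named. The Data collection section describes the list differently: variable blocks of four to eight, with no mention of stratification.

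**Primary test.** The Analysis section states: "A two-sample two-sided test of proportions will be used to assess the primary outcome of loneliness". Nothing in that sentence stratifies or adjusts.

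**Second analysis of the same outcome.** The section adds that improvement in De Jong category "will be assessed using a logistic regression model, and results will be reported as odds ratios". The covariates appear only as unnamed confounders, for example in the missing-data rule: "participants with more than 15% missing data for confounding variables will be excluded from the analysis". They pass through a variance inflation screen that keeps one of any two highly correlated variables. Referral source is not mentioned.

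**Who is recruited.** The Abstract names two EDs. Study design and setting, and Recruitment and training, add a family medicine centre. Table 2 adds geriatric clinics. Inclusion and exclusion criteria go further: "We will accept referrals from participating ED and clinics as well as self-referrals from participants to improve recruitment". The Discussion describes the aim as "reducing SIL for the older adult population after discharge from the ED", and the scientific title in Table 2 likewise ties the programme to ED discharge.

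**The concern.** Stratified allocation balances the arms within each referral source. If improvement differs between sources, that balance removes some chance variation from the treatment comparison. A test that ignores the strata still counts that variation in its standard error. The precision bought by the design is then not used, in a trial with 47 participants per arm.

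An unseen analysis plan does not settle this, because the article itself states the primary test. Nor does the logistic model cure it as written. It is not said to replace the test, its covariates are not listed, and the collinearity screen could drop a design factor.

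Referral source is also the variable that separates ED patients from clinic and self-referred participants, so it bears on which population the pooled estimate describes. That is a secondary matter of wording and reporting.

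**Working it through.** **Inputs from the protocol article.** 47 per arm; control improvement up to 15%; detectable difference up to 28.1 points, so 15% versus 43.1%; power above 80%. **Assumed:** two-sided alpha of 0.05 (the sample size section gives none), the share of each referral source, and improvement rates by source. The documents give neither shares nor rates by source.

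**1. The plan's own figure.** With p0 = 0.15, p1 = 0.431, mean 0.2905 and d = 0.281:

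n = [1.960·√(2·0.2905·0.7095) + 0.842·√(0.15·0.85 + 0.431·0.569)]² / 0.281² = (1.258 + 0.514)² / 0.0790 = 39.8, so 40.

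With continuity correction: (39.8/4)·[1 + √(1 + 4/(39.8·0.281))]² = 46.6, so **47**, as stated. Without the correction, power at 47 per arm is 86.3%. This is the upper end of the stated range and the planning point used below.

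**2. Why the unstratified test is conservative.** With arms balanced within strata of share w and rate p, the true null variance of the difference is (2/n)·Σw·p(1−p). The unstratified test uses (2/n)·p̄(1−p̄), which is larger by (2/n)·Σw(p−p̄)². Take 24, 12 and 11 participants per arm in three sources (w = 0.511, 0.255, 0.234):

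- Rates 8/15/30%: p̄ = 0.149 and p̄(1−p̄) = 0.1271. The between-source part is 0.511·0.069² + 0.234·0.151² ≈ 0.0078, about 6% of the variance used.
- Rates 4/16/37%: p̄ = 0.148 and p̄(1−p̄) = 0.1260. The between-source part is about 0.0175, or 14%.
- Equal rates: zero.

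**3. Power at 15% versus 43.1%.** Simulation with 200,000 or more trials per case, 47 per arm, exact balance within strata, a common odds ratio for treatment, and an average control rate of 15%. The first row uses two equal strata; the others use 24/12/11.

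| Control rates by source | Unstratified | Mantel-Haenszel | Gain (points) |
|---|---|---|---|
| no difference | 87.1% | 86.9% | −0.2 |
| about 12/15/20% | 87.3% | 87.3% | 0 |
| about 10/15/25% | 87.6% | 88.2% | 0.6 |
| about 8/15/30% | 87.9% | 89.4% | 1.5 |
| about 4/16/37% | 89.6% | 93.1% | 3.5 |

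Unstratified power stays above 80% in every row.

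**4. Type I error.** With two equal strata and a common rate of 29%, the unstratified test rejects 5.1%, 4.9%, 4.4% and 3.8% of the time for between-stratum odds ratios of 1, 2, 3 and 5. Mantel-Haenszel stays at about 5%. At a common rate of 15% with no stratum effect, the unstratified test runs at about 5.5%. That comes from the normal approximation with small counts, not from ignoring strata, and it falls as the stratum effect grows (4.7% at odds ratio 5).

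**The case against.** **The loss is small and on the safe side.** This stands. A prognostic stratum makes the test reject too rarely, not too often. A reader might infer that ignoring the stratification inflates false positives or leaves 47 per arm too few; the calculations support neither.

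**Much larger losses can be produced.** With control rates of 5/20/45% by source and a treatment odds ratio of 3.3, unstratified power is about 51% against 60% for Mantel-Haenszel, with type I error 3.3% against 4.9%. This should not be read as the expected cost. The average control rate is (24·5 + 12·20 + 11·45)/47 = 18.2%, above the 15% ceiling in the sample size section. The odds ratio between extreme sources is (0.45/0.55)/(0.05/0.95) = 15.5, and the overall treatment difference is only 18.0 points rather than 28.1.

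**Nothing shows that source is prognostic.** Correct. The mismatch between design and test is certain; the consequence is conditional.

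**An adjusted model is already planned.** Also correct, and its covariate list may be set in an analysis plan that is not shown. It would be wrong to say that no adjusted estimate is foreseen. But this does not alter the primary test that the article states.

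**The population point is separate.** Largely right. A reader might infer that self-referred participants never attended an ED. Self-referral is only a route of entry, and Table 2 still requires care from the ED or clinics at the participating sites. The section headed Conclusions does not mention the ED; the claim lies in the title and Discussion. What remains is that the lists of settings disagree and that clinic patients are admitted to a trial described as post-ED.

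**Conclusion.** The point holds as a modest one about efficiency and coherence. The stated primary test ignores the only factor on which allocation is stratified. At 15% versus 43.1% the cost is about 0 to 1.5 points of power for moderate source effects, about 3.5 for a very strong one, and none if source is not prognostic. Trial validity and the sample size are unaffected. The direction follows from the algebra, provided the arms are in fact balanced within source. The size rests on assumed shares and rates by source and on a two-sided 5% level.

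That proviso is itself open, since one of the two accounts of the randomisation list does not mention strata. The recruitment-setting mismatch is real but secondary, and does not by itself show that the pooled estimate is wrong for ED patients.

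**What to change.** 1. Reconcile Randomization and blinding (blocks of three, stratified) with Data collection (blocks of four to eight, strata not mentioned), so that the analysis follows the list actually used. Define the levels of referral source, for example ED, clinic and self-referral.
2. If the list is stratified, replace the unstratified test for each primary contrast with a Mantel-Haenszel test by referral source. Alternatively, make the planned logistic regression primary, with arm and referral source as fixed terms exempt from the collinearity screen. State in advance that sparse levels are pooled as ED versus non-ED.
3. List the same recruitment settings in the Abstract, Table 2, Study design and setting, Recruitment and training, and Inclusion and exclusion criteria. Either report the estimate in ED-recruited participants beside the pooled one, or describe the target population in the title and Discussion as including clinic and self-referred participants.

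The cost is wording only. Stratified allocation already requires referral source to be recorded, and no additional participants are needed. The one drawback is that small strata may have to be pooled.

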### Intervention

Following randomization, research assistants will attempt to match volunteers and participants based on (1) any gender preferences and (2) shared interests or hobbies. This matching process will serve to promote adherence to intervention protocols as will the standardized 3-h volunteer training session which will teach strategies for volunteers to encourage participant engagement. Finally, we have attempted to minimize the research burden on participants to further limit potential contributors to nonadherence. For example, there is no interim data collection between enrollment and completion of the study. We are monitoring adherence by logging the time and duration of phone calls between volunteers and participants. Note, as the study’s intervention is a social interaction and not a pharmaceutical trial, drug tablet returns and laboratory tests are not applicable.

#### Same-generation peer support intervention

The same-generation peer support intervention group will receive the current HOW R U? intervention delivered by similarly aged peer volunteers. The HOW R U? intervention consists of weekly 30-min telephone-support calls over 12 weeks. The focus of each interaction is a strength-based approach including encouraging the participant to identify goals to improve SIL such as integrating with community activities [4]. Volunteers will reassess these goals each week and will maintain progress logs for each participant consisting of session dates, session duration, sessions missed, and any participant drop-outs.

#### Intergenerational intervention

The intergenerational intervention group will receive the HOW R U? intervention over the telephone as described above and delivered by trained intergenerational volunteers. Unique to the intergenerational intervention, informal service-learning goals will be assigned to the student volunteers and simultaneously made known to their participants. These include reflecting on the older adult’s experience of navigating the healthcare system, identifying negative ageist perceptions and stereotypes associated with older adults and the aging process, and risk factors for SIL among older adults. The purpose of these additional objectives is to facilitate a sense of mutual benefit and self-perceptions of generativity in the older adult participants consistent with Erikson’s theory [16].

#### Waitlist control

The current standard of care is not to offer interventions for SIL. Thus, participants randomized to the control group will be assigned to a 24-week waitlist and not receive any interventions. Following the assessment of primary and secondary outcomes after a 24-week period, control group participants will exit the current trial but will be offered their choice of the intergenerational or same-generation peer support HOW R U? intervention. There are no other criteria specified in this trial for concomitant care that is permitted/prohibited.

#### Criteria for discontinuing or modifying interventions

As this is a minimal-risk study, no modification or discontinuation of interventions is anticipated. Participants voluntarily participate in the intervention and can withdraw their consent and exit the study at any time. There are currently no established criteria for modifying allocated interventions for a given trial participant.

### Data collection

Research assistants will collect data for all groups over the telephone. Initial screening of potential participants by research staff involves the six-item De Jong loneliness scale which is described in further detail below. We will then collect demographic data including age, gender, living arrangement, pet ownership, educational attainment, technology profile index (modified), and baseline assessments of primary and secondary outcomes (see the “Outcome measures” section) from eligible participants who provide informed consent. Trained research staff will obtain verbal informed consent for this study as approved by all participating institutional REBs (see Appendix 2 for the informed consent model). Research staff are not involved in the clinical management of participants to avoid the perception of coercion. In order to allocate patients to specific arms, a statistician independent of the trial management will use a computer procedure to generate a variable block randomization list with blocks varying between four and eight. Note, as in our previous trial, research staff involved in outcome assessment will be blinded to randomization status. After completion of the 12-week intervention, research assistants will reassess outcomes within 2 weeks (study week 12–14) and 12 weeks (study week 24). To minimize the potential Hawthorne Effect, study endpoints will be collected only upon completion of the intervention [17]. Personal health information is removed from all study databases. Deidentified data will be stored in a password-protected computer accessible only by the study’s research assistants and corresponding author and will remain confidential. As this is a minimal-risk study, no formal data monitoring committee was required by our REB. A study committee consisting of the principal investigator, coauthors, and statistician will have regular meetings once a quarter to discuss ongoing data collection, quality, and outcomes. Note, no interim analyses are planned in this minimal-risk study.

### Outcome measures

The primary outcome is loneliness as measured using the six-item De Jong loneliness scale after completion of the intervention (weeks 12–14 of the study). The De Jong scale has been extensively validated in older populations and is divided into four clinically relevant categories: 6—severe loneliness, 4–5—moderate-to-severe loneliness, 2–3—low loneliness, and 0–1—no loneliness [12].

The secondary outcomes are the following: (1) the de Jong loneliness Scale at 12 weeks post-completion of the intervention to assess sustainability (study week 24); (2) six-item Lubben’s Social Network Scale [18]; (3) five-item Geriatric Depression Scale to assess mood [19]; (4) Brief Alzheimer’s Screening Test to assess baseline cognitive performance [20]; (5) EQ-5D-5L to assess perceived health-related quality of life in the areas of self-care, mobility, usual activities, pain/discomfort, and anxiety/depression [21]; (6) the Older Americans Resource Scale to assess functional status [22]; (7) the Loyola Generativity Scale to assess generativity [23]; (8) perceived benefit by the participant; and (9) benefit to the volunteer as perceived by the participant. The standardized measurement instruments selected for the trial have been extensively validated in older adults. The Loyola Generativity Scale has demonstrated good interrater reliability as well as responsiveness in trials of older adults [24, 25]. To assess the secondary outcome of participant preference for same-generation peer support versus intergenerational HOW R U? intervention, we will use a 5-point Likert scale with the following options: “I strongly prefer peer support,” “I prefer peer support,” “neutral,” “I prefer intergenerational,” and “I strongly prefer intergenerational”. Please see Appendix 3 for full details.

### Sample size and power

Each group will consist of a sample of 47 subjects which will detect a 13.9–28.1% difference between the treatment and control groups in the proportion of people who improve by one category (e.g., from severe loneliness to moderate-to-severe loneliness) with a power greater than 80%. This assumes that up to 15% of control group participants may have a spontaneous improvement in loneliness categories. With these sample sizes, three comparisons may be made: intergenerational intervention to the control group, same-generation peer support intervention to the control group, and intergenerational to the same-generation peer support intervention.

### Analysis

All analyses will use SAS Version 9.4 (SAS Institute, Cary, NC, USA). A two-sample two-sided test of proportions will be used to assess the primary outcome of loneliness in the control group versus the intergenerational HOW R U?, and the control group versus the same-generation peer support HOW R U? intervention. Improvements in the binary outcome of the loneliness category of the De Jong Loneliness Scale will be assessed using a logistic regression model, and results will be reported as odds ratios with the corresponding 95% confidence intervals. The variance inflation factor (VIF) will be calculated to assess for multicollinearity before the logistic regression model is built such that if two variables are highly correlated (i.e., VIF > 4 or tolerance < 0.25), only one of the two variables is retained for the final model. To compare the secondary outcomes, they will be reported as means with corresponding 95% confidence intervals.

Potential missing data will be managed as follows. For logistic regression, participants with more than 15% missing data for confounding variables will be excluded from the analysis. Note that in the main trial, less than 5% of participants would have been excluded. For participants with less than 15% missing data, we will use imputation for confounding variables. Participants with missing outcome data will be excluded from analysis (i.e., lost to follow-up). Note that after two-thirds of the participants have been enrolled, we will assess the loss-to-follow-up rate and adjust the enrollment accordingly. For example, if the lost-to-follow-up rate is 20%, we will increase the enrolment by 20%. To manage protocol nonadherence, participants will be analyzed using intention-to-treat analysis regardless of their adherence to the protocol.

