### Study purpose

Our primary outcomes are to assess whether the intergenerational HOW R U? intervention (1) reduces SIL more than the waitlist control group at study week 12 and (2) reduces SIL more than the current same-generation peer support HOW R U? intervention at study week 12.

Secondary outcomes include assessing:The impact of the intergenerational HOW R U? intervention on (i) SIL at study week 24, (ii) depression, (iii) quality of life, (iv) functional status, (v) generativity, (vi) participant’s perceived self-benefit, and (vii) participant’s perceived benefit for the volunteer delivering the HOW R U? intervention at study weeks 12 and 24.Participant stated preferences for intergenerational versus same-generation peer support HOW R U? intervention prior to randomization. Note, participants will be randomized regardless of their intervention preference.

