### Hypotheses

Our primary hypothesis is that participants who receive the intergenerational HOW R U? intervention will have superior outcomes compared to the waitlist control group and to the same-generation peer support HOW R U? intervention. Our second hypothesis is that participants with higher perceptions of generativity will have greater reductions in SIL. Third, we hypothesize that participants in the intergenerational intervention will have higher perceptions of generativity after 12 weeks than the same-generation peer support and waitlist control groups.

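### The second primary comparison, intergenerational versus same-generation peer support, has no assigned primary test; the Analysis section names peer support versus control in its place

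*Protocol article*

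**What the plan says.** Under Study purpose, the first primary aim of the protocol article is to learn whether the intergenerational intervention "reduces SIL more than the waitlist control group at study week 12". The second aim is to learn whether it "reduces SIL more than the current same-generation peer support HOW R U? intervention at study week 12". The Hypotheses section repeats both as the primary hypothesis: intergenerational participants "will have superior outcomes compared to the waitlist control group and to the same-generation peer support HOW R U? intervention".

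The Analysis section then fixes the primary test, a two-sided comparison of two proportions, and gives its contrasts as "in the control group versus the intergenerational HOW R U?, and the control group versus the same-generation peer support HOW R U? intervention". The next sentence says that improvement in loneliness category "will be assessed using a logistic regression model, and results will be reported as odds ratios with the corresponding 95% confidence intervals". It names no contrast and no reference arm.

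The Sample size and power section gives 47 per group. It states power above 80% for a difference of 13.9 to 28.1% between treatment and control, with up to 15% of controls improving spontaneously. It then lists three comparisons that the sample permits, the last being "and intergenerational to the same-generation peer support intervention". It ranks none of them and gives no power for that one.

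**The concern.** The objectives and the primary test share only one contrast, intergenerational versus control. The second primary objective has no test assigned to it, and one of the two named primary tests answers a question that the protocol does not list as primary.

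This is more than a detail left to an analysis plan, because the article does name its contrasts and they disagree with its objectives. An analysis plan faithful to the Analysis section would omit the second objective, and one faithful to Study purpose would contradict the Analysis section. Which contrasts count as primary could then be settled after the results are known.

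A report limited to the two tests against control also invites a familiar error: reading significance in one arm and not in the other as evidence that the arms differ.

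**Working it through.** **1. The contrasts side by side**

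| Contrast | Study purpose and Hypotheses | Sample size and power | Test named in Analysis |
|---|---|---|---|
| Intergenerational vs control | Primary | Power stated | Yes |
| Intergenerational vs peer support | Primary | Listed as possible, no power stated | No |
| Peer support vs control | Not listed as primary | Power stated | Yes |

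**2. Reproducing 47 per arm**

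Inputs from the sample size section: control 15%, difference 28.1 points (so 43.1% on treatment), power 80%. Two-sided alpha 0.05 is assumed from the 95% confidence intervals, since the article states no alpha. The mean proportion is p̄ = 0.2905.

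n₀ = [1.96·√(2p̄(1−p̄)) + 0.842·√(p₁(1−p₁) + p₂(1−p₂))]² / d²
= [1.96·0.642 + 0.842·0.611]² / 0.281² ≈ 39.8, so 40 per arm.

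With the continuity correction, n = (n₀/4)·[1 + √(1 + 4/(n₀d))]² = 9.94 × 2.165² ≈ 46.6, so 47 per arm. This matches the plan exactly and confirms that the sample was sized against control. The lower figure of 13.9 points cannot be checked because its control rate is not given; nothing here depends on it.

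**3. What 47 per arm gives for the head-to-head**

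Power = Φ[(d − 1.96·√(2p̄(1−p̄)/47)) / √((p₁(1−p₁) + p₂(1−p₂))/47)], without continuity correction. The article gives no peer-support rate, so these rates are assumptions.

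| Assumed peer rate | Gain detectable with 80% power | Power for a 13.9-point gain |
|---|---|---|
| 15% | 25.6 points | 37% |
| 20% | 26.9 | 33% |
| 28.9% | 28.3 | 29% |
| 35% | 28.5 | 27% |
| 43.1% | 28.2 | 27% |
| 50% | 27.4 | 27% |

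Check at 35%: d = 0.285 and p̄ = 0.4925, so (0.285 − 0.202)/0.0989 ≈ 0.84 and Φ ≈ 0.80.

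**4. What follows if the two tests against control are compared instead**

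Control improves at 15% and both active arms improve at the same rate (assumed). Given the control count c, the two active arms are independent, so

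P(intergenerational significant, peer not) = Σ P(C = c) · P(intergenerational significantly better | c) · [1 − P(peer significant | c)].

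Exact enumeration with the uncorrected pooled z test, two-sided 0.05, 47 per arm:

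| Both active arms | Each vs control significant | Intergenerational significant, peer not | Direct test favours intergenerational |
|---|---|---|---|
| 30% | 42% | 16% | about 2.5% |
| 35% | 62% | 16% | about 2.5% |
| 43.1% | 87% | 8.5% | about 2.5% |

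The two arms do not differ in any row, so the last two columns are rates of a false impression of superiority.

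**The case against.** A reader might infer that the trial cannot answer its second primary question. The documents do not support that. The arms are randomised in parallel with the same outcome, timing and blinded assessors, and the sample size section lists the head-to-head comparison. The logistic model with arm as a three-level factor would yield that contrast with its own odds ratio and interval. Contrast coding is commonly left to the analysis plan.

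A reader might also infer that the authors intend to judge the two interventions by comparing significance against control. No section says so; the 8.5% to 16% is conditional on someone doing it.

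Both points limit the concern without removing it. Listing a comparison as possible gives it neither a test nor primary status. A logistic model with no stated contrast could supply the head-to-head, but nothing commits to it. The one sentence that does name contrasts for the primary outcome leaves it out.

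It is also fair to object that naming the head-to-head as primary installs a weakly powered test. That is correct, and it is why the fix must include the power statement.

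**Conclusion.** The concern stands as an internal contradiction. One of the two primary objectives has no assigned primary test, and one of the two named tests serves no primary objective. The comparison can still be made from the trial's data, so the fault lies in the specification and not in the design. It should be corrected before outcomes are examined by arm.

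The contradiction itself rests on the text alone. The size figures rest on assumptions: two-sided 0.05, full follow-up of 47 per arm, control improvement of 15%, and active-arm rates that the article does not supply. On those assumptions, comparing the two tests against control would suggest a non-existent advantage in about 8.5% to 16% of trials, against about 2.5% for a direct test. The head-to-head reaches 80% power only for a gain of about 26 to 28 points over peer support, which is as large as the upper end of the effect planned against no intervention.

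**What to change.** - In the Analysis section, name intergenerational versus waitlist and intergenerational versus same-generation peer support, both at week 12, as the primary tests.
- Give peer support versus waitlist a stated status, for example secondary.
- Estimate all three contrasts from one three-arm logistic model, each with a 95% confidence interval.
- State alpha and how it is handled across the two primary tests. If success is claimed only when both are significant, each can be tested at the full level; if either alone suffices, an ordering or an adjustment is needed. An equal split to 0.025 would raise the head-to-head gain detectable with 80% power, by the same formula, to 28.5 points at a 15% peer rate.
- State that 47 per arm gives 80% power for the head-to-head only for a gain of about 26 to 28 points (assumed peer rates 15% to 50%, uncorrected two-sided 0.05).

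The cost is wording in the protocol and the analysis plan, with no extra participants or data. The downside is that the stated power for the second primary objective will look less favourable than the figure now given against control.
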